## Abstract

**Background::**

Primary care providers (PCPs) are expected to help patients with obesity to lose weight through behavior change counseling and patient-centered use of available weight management resources. Yet, many PCPs face knowledge gaps and clinical time constraints that hinder their ability to successfully support patients’ weight loss. Fortunately, a small and growing number of physicians are now certified in obesity medicine through the American Board of Obesity Medicine (ABOM) and can provide personalized and effective obesity treatment to individual patients. Little is known, however, about how to extend the expertise of ABOM-certified physicians to support PCPs and their many patients with obesity.

**Aim::**

To develop and pilot test an innovative care model – the Weight Navigation Program (WNP) – to integrate ABOM-certified physicians into primary care settings and to enhance the delivery of personalized, effective obesity care.

**Methods::**

Quality improvement program with an embedded, 12-month, single-arm pilot study. Patients with obesity and ≥1 weight-related co-morbidity may be referred to the WNP by PCPs. All patients seen within the WNP during the first 12 months of clinical operations will be compared to a matched cohort of patients from another primary care site. We will recruit a subset of WNP patients (*n* = 30) to participate in a remote weight monitoring pilot program, which will include surveys at 0, 6, and 12 months, qualitative interviews at 0 and 6 months, and use of an electronic health record (EHR)-based text messaging program for remote weight monitoring.

**Discussion::**

Obesity is a complex chronic condition that requires evidence-based, personalized, and longitudinal care. To deliver such care in general practice, the WNP leverages the expertise of ABOM-certified physicians, health system and community weight management resources, and EHR-based population health management tools. The WNP is an innovative model with the potential to be implemented, scaled, and sustained in diverse primary care settings.

## Background

Excess body weight (ie, overweight and obesity) is a leading cause of morbidity and mortality (Prospective Studies Collaboration, 2009) as well as a major risk factor for severe illness and death from the novel coronavirus 2019 (Popkin *et al.*, 2020). Modest weight loss of ≥5% body weight can help individuals with overweight or obesity to prevent, manage, or reverse weight-related chronic conditions (Anderson & Konz, 2001; Diabetes Prevention Program Research Group, 2009; Garvey *et al*., 2012; Rothberg *et al.*, 2017), and reduce individuals’ annual medical care costs by over $2,000 (Cawley *et al*., 2015). Due to the human and economic costs of obesity, health policies support the use of evidence-based obesity treatments (eg, weight loss surgery and lifestyle change programs) and intensive behavioral counseling by primary care providers (PCPs) (Kahan & Zvenyach, 2016). Moreover, clinical practice guidelines encourage PCPs and their practices to play central roles in obesity management (Final Recommendation Statement: Weight Loss to Prevent Obesity-Related Morbidity and Mortality in Adults: Behavioral Interventions - US Preventive Services Task Force, 2003; Jensen *et al.*, 2014), and the patient-centered medical home model provides an ideal context to deliver team-based, coordinated, and longitudinal obesity care (Bernstein *et al.*, 2016).

Despite these initiatives and opportunities, patients with obesity often receive suboptimal weight management in general practice settings due, in part, to provider- and practice-level factors (Tsai & Wadden, 2009). Such factors include most PCPs’ lack of specialized training in obesity treatment, brief office visits with competing clinical demands, and strained clinic capacities, which preclude frequent weight-focused visits (Cabana *et al*., 1999; Foster *et al.*, 2003; Tsai & Wadden, 2009; Salinas *et al*., 2011; Wadden *et al.*, 2014; Ossolinski *et al.*, 2015; Phelan *et al*., 2015; Mainous *et al*., 2016; Morris *et al.*, 2016; Petrin *et al.*, 2017; Nhim *et al.*, 2018). Thus, PCPs commonly recommend general diet and physical activity changes rather than specific obesity treatment and follow-up plans (Bardia *et al.*, 2007; Alexander *et al.*, 2011; van Dillen *et al*., 2013; Tseng *et al*., 2017). Most PCPs, for example, seldom prescribe anti-obesity medications (Saxon *et al.*, 2019) or initiate bariatric surgery referrals (Falvo *et al*., 2018; Pearce *et al*., 2019). Additionally, most general practice settings lack population health management strategies to identify and support individuals who do not meet weight loss goals (Baer *et al*., 2020). Yet, such strategies could be an important way to optimize patients’ weight loss outcomes, as individuals who do not achieve early weight loss (eg, within 12 weeks) with one approach are unlikely to lose weight without additional support or a completely different treatment (Elfhag & Rössner, 2010; Handjieva-Darlenska *et al.*, 2010; Kong *et al.*, 2010; Waring *et al.*, 2014; Miller *et al*., 2015; Unick *et al.*, 2015; Fitzpatrick *et al.*, 2018; Tronieri *et al.*, 2018).

To close knowledge gaps and more effectively help patients lose weight, a growing number of physicians – primarily those specialized in Internal Medicine and Family Medicine – are obtaining certification in obesity medicine through the American Board of Obesity Medicine (ABOM) (Kushner *et al*., 2017). The ABOM was established in 2011 to advance the delivery of evidence-based obesity care. Physicians who complete specific educational requirements and pass a standardized examination become ABOM Diplomates (hereafter referred to as ‘Diplomates’). In 2020, there were 4,152 Diplomates throughout the United States, and 65% were either Family Medicine or Internal Medicine providers (Stats and Data, n.d.). Diplomates are trained to deliver guideline-adherent obesity management care using a broad range of evidence-based resources (eg, anti-obesity pharmacotherapy, nutrition therapy, and bariatric surgery referral) (Gudzune *et al*., 2021). ABOM Diplomates may be a valuable resource in primary care settings, particularly if their expertise can be extended to support other PCPs and their many patients with obesity.

One potential strategy to extend the reach of ABOM Diplomate expertise may be through a team-based, collaborative care approach in which ABOM Diplomates serve as expert consultants to enhance PCPs’ delivery of evidence-based obesity care. Collaborative Care Models (CCMs) are widely used in primary care settings to improve outcomes among patients with other complex chronic conditions through patient self-management support, provider guideline dissemination and education, delivery system redesign such as team-based care, and use of population health management strategies using clinical informatics (Coleman *et al*., 2009; Yeoh *et al*., 2018). Building upon these components, the highly effective CCM for mental health conditions aims to improve outcomes for patients with depression by integrating mental health experts into the primary care team (Press *et al.*, 2017). Specifically, patients work with primary care team members (eg, PCPs, care managers) to develop initial treatment plans. Care managers then use population health management tools proactively to monitor patients’ symptoms (eg, change in depression scores) and facilitate timely intervention such as PCP follow-up or consultation with a mental health provider for patients who may need additional support (Press *et al*., 2017).

Little is known about the potential weight loss effectiveness of a collaborative care approach to obesity treatment (Ma *et al*., 2019; Lv *et al*., 2020). Prior work testing a collaborative care approach for patients with depression and obesity demonstrated modest weight loss at 12 months, though the majority of participants did not achieve clinically significant weight loss (Ma *et al*., 2019; Pagoto *et al*., 2013). Suboptimal weight loss may have been due, in part, to use of a one-size-fits-all lifestyle change program rather than personalized obesity treatment and follow-up plans (Lv *et al*., 2020).

Our team aims to develop and pilot test an innovative care model – the Weight Navigation Program (WNP) – to integrate Diplomates into primary care settings, enhance delivery of personalized obesity treatment, and successfully help more patients to achieve ≥5% body weight loss (versus traditional care models) while reducing burden on individual PCPs. The aim of this paper is to describe the design, rationale, and planned evaluation for the WNP. We hypothesize that the program will be feasible and acceptable among patients and providers. We also hypothesize that patients who engage in the WNP will achieve greater weight loss than a contemporaneous matched cohort of patients from another primary care clinic with similar sociodemographic characteristics.

### WNP team members and stakeholders

The Weight Navigation Program (WNP) team consists of an Endocrinologist (AK; Program Director), a Family Medicine physician and ABOM Diplomate (AO; Medical Director), an Internal Medicine physician-researcher and ABOM Diplomate ([name]; Research Director), a clinical project manager (CD), a research project manager, a clinic scheduler, and a medical assistant. The Program Director interfaces with institutional stakeholders, including representatives from the programs shown in Table 1, coordinates personnel training, and directs program implementation. The Medical Director interfaces with PCP colleagues, leads informational talks about the WNP and referral criteria, and provides clinical care for WNP patients; she is referred to as the Weight Navigator (WN) hereafter. The Research Director leads efforts to refine and evaluate the effects of the WNP.

**Table 1. tbl1:** A summary of locally available weight management resources

Health system resources to support weight control	
Nutrition Services	Registered Dietitians (RD) are available to provide personalized diet recommendations
MHealthy	Available to health system-employed faculty and staff Includes a range of classes, programs, and resources that assist with lifestyle improvement efforts (eg, eating habits, weight control, and healthy lifestyle change)
Metabolic Fitness Program	Offered through Preventative Cardiology Provides a cardiovascular disease risk assessment and then provides exercise, nutrition, stress management, and behavior change strategies to risk Group-based program with virtual option for participation 24 weeks in duration
Obesity & Metabolic Disorders Program	Offered through The Division of Metabolism, Endocrinology, and Diabetes to patients with obesity and at least one other metabolic disorder (eg, type 2 diabetes, polycystic ovarian syndrome) Includes a comprehensive history, physical, genetic screening, and laboratory assessment to guide individualized and multi-component treatment plans.
Weight Management Program	Evidence-based, medically supervised, intensive medical behavioral program that utilizes meal replacement 2 or more years in duration Individuals work with endocrinologists and dietitians to achieve and maintain ≥10%–15% weight loss
Endoscopic Bariatric Therapy	Endoscopic procedures performed by gastroenterologists with specialized training Designed for individuals who are not candidates for weight loss surgery or who prefer a less-invasive, non-surgical alternative.
Bariatric surgery	Laparoscopic sleeve gastrectomy or Roux-en-Y-gastric bypass options are available. Michigan Medicine program consists of a multidisciplinary care team that includes surgeons, physician assistants, registered dietitians, neuropsychologists, endocrinologists, and nurses; all team members have completed specialized training.
Post-bariatric Endocrinology	All patients undergoing bariatric surgery at the institution are offered ‘lifelong’ follow-up in the long-term care clinic. The clinic also serves as a referral center for patients experiencing long-term complications even if the surgery was performed elsewhere. Team of endocrinologists and dietitians with expertise in obesity and bariatric care who conduct medical assessments, laboratory monitoring (eg, vitamin/mineral levels), behavior change counseling, and initiation of weight loss pharmacotherapy medical or subspecialty referrals, if needed
Resource to support diagnosis of weight-related conditions and inform treatment plan recommendations	
Non-Alcoholic Fatty Liver Disease (NALFD) Clinic	Hepatologists diagnose NAFLD, monitor patients over time, and provide treatment recommendations, which include weight loss and dietary modification.
Lipodystrophy and Atypical Diabetes Clinic:	Special expertise provided by the endocrinologist in the Lipodystrophy/Atypical Diabetes Clinic allows for the identification and treatment of these rare conditions.
Obesity hypoventilation clinic	Sleep Medicine specialists can diagnosis this condition and recommend specific treatment
Metabolism, Endocrinology & Diabetes (MEND) Clinic	Endocrinologists in the MEND clinic screen for secondary hormonal causes of obesity.

Key representatives from the weight management and evaluation subspecialty groups shown in Table 1 facilitated a brief training experience for the Weight Navigator to gain knowledge in the full spectrum of health system and community weight management resources. Over the course of 3 months, the Weight Navigator spent time with team members from the various groups to learn the details of each program’s eligibility criteria, goals, and operations, thus enabling her to better guide patients’ informed treatment choices.

### Study design

This is a clinical quality improvement project with an embedded single-arm pilot study. Specifically, patients with obesity who desire to lose weight will be referred by their PCP to the WNP. Patients scheduled for a WNP appointment will be offered the opportunity to participate in research; we will aim to recruit 30 participants to the research arm of the study Research activities include (1) surveys at 0, 6, and 12 months; (2) optional semi-structured interview participation at 0 and 6 months; and (3) use of a text messaging program for remote weight monitoring.

### Study setting

Michigan Medicine is a large, academic medical center that includes 14 adult primary care clinics throughout southeast Michigan that serve approximately 240 000 patients. The pilot Weight Navigation Program will be initiated at a single Michigan Medicine primary care site. Michigan Medicine also offers diverse resources for the evaluation and management of obesity and obesity-related chronic conditions (Table 1). Despite the availability of these programs, unpublished survey data of PCPs in our health system (*n* = 107) demonstrate that most providers refer patients with obesity to a dietitian (*n* = 89, 83%) while only a minority utilize other resources such as medical weight management (*n* = 23, 21.5%) or weight loss surgery (*n* = 20, 18.7%).

### Participants WNP eligibility

Primary care patients with a body mass index (BMI) ≥ 30 kg/m^2^ and at least one weight-related chronic condition (eg, type 2 diabetes, hypertension, hyperlipidemia, non-alcoholic fatty liver disease, obstructive sleep apnea) may be referred by their PCP to the WNP. WNP exclusion criteria include primary care received at a location other than the pilot clinic site and pregnancy or breastfeeding. Patients may be scheduled for a WNP appointment regardless of insurance type. However, patients’ eligibility and out-of-pocket costs for obesity treatments may differ based on insurance status; this will be taken into consideration by the Weight Navigator when working with patients to develop personalized treatment plans.

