#### Clinical impact of the WNP

##### Change in weight

We will abstract weight and height data from the EHR for all WNP patients who complete a clinic visit within the first 12 months of clinical program operations. We will evaluate average weight change among WNP patients during the 12 months following their WNP appointment. We will also identify a contemporaneous cohort of patients with obesity matched by gender and approximate age (within 10 years) to WNP patients. The matched cohort will be selected from another Michigan Medicine primary care clinic located less than 1 mile from the pilot site clinic and serving a similar patient population. We will compare between-group weight change among WNP patients and the matched cohort. In addition to evaluating mean weight change, we will also evaluate achievement of ≥5% body weight loss.

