##### Patients’ engagement with health system weight management resources

We will compare the rate of engagement in health system weight management resources among WNP patients as compared to patients in the matched cohort.

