### Limitations and opportunities

This program has several potential limitations. First, it will be implemented at a single site and thus may not be generalizable to all practice settings. However, we believe the WNP model offers a conceptual and practical framework that may be successfully adapted to diverse primary settings where at least one physician is certified in obesity medicine. Second, cost barriers may impede patients’ use of certain weight management resources. Fortunately, there is growing insurance coverage for weight management services (Jannah *et al.*, 2018), drug discount programs support the use of some anti-obesity medications (Prescription Prices, Coupons & Pharmacy Information – GoodRx, n.d.), and most health plans cover nutrition counseling services. Moreover, we will utilize low-cost, community-based resources such as Diabetes Prevention Programs when developing personalized obesity treatment plans. Fourth, some components of the current WNP model (eg, MPOTA-WM outreach) require research funding, which may limit implementation in general practice settings. However, to the extent possible, the WNP model uses billable services, and we will aim to identify opportunities to integrate MPOTA-WM into routine clinical care. Moreover, remote monitoring tools are now common features of many EHR systems, reimbursement guidelines encourage use of such tools (Final Policy, Payment, and Quality Provisions Changes to the Medicare Physician Fee Schedule for Calendar Year 2021 | CMS, (n.d.), and additional policy changes on the horizon may enable more providers to play active roles supporting patients with obesity (Cassidy, 2019).

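### Insurance is named as a possible influence on access to obesity treatment, but the comparison cohort is matched on gender and age only and no adjustment for insurance is stated (minor)

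*Protocol article*

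**What the plan says.** Under Participants WNP eligibility, the article states that "Patients may be scheduled for a WNP appointment regardless of insurance type", and then that "eligibility and out-of-pocket costs for obesity treatments may differ based on insurance status". The Weight Navigator is to take this into account when planning treatment. Limitations and opportunities adds that "cost barriers may impede patients’ use of certain weight management resources". Table 1 describes one listed resource, MHealthy, as "Available to health system-employed faculty and staff".

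The comparison cohort is defined in the Change in weight subsection of Clinical impact of the WNP: a "contemporaneous cohort of patients with obesity matched by gender and approximate age (within 10 years) to WNP patients". It comes from another clinic of the same health system, under a mile away and described as having comparable patients.

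The following subsections compare the two cohorts on referrals, engagement, prescriptions and refills. The engagement entry begins "We will compare the rate of engagement in health system weight management resources among WNP patients". Quantitative data analysis specifies a difference-in-difference approach for weight and names no covariates. Insurance does not appear anywhere as a matching, stratification or adjustment variable.

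**The concern.** The article itself identifies a patient characteristic that may determine which treatments are available and at what price. It then compares two non-randomized cohorts on receipt of those treatments, under a matching rule that leaves the characteristic out. Engagement, prescriptions and refills are the outcomes that coverage limits most directly.

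If coverage mix or the share of health-system employees differs between the cohorts, part of that difference would be reported as clinical impact of the program, or would mask a real effect. This could happen even if entry criteria and the start of follow-up were perfectly aligned.

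The article hypothesizes greater weight loss than in the matched cohort, and it intends to refine the program and plan a larger trial from these data. A distorted comparison would therefore have some consequence.

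**Working it through.** The plan gives no figure to reproduce: no coverage shares, no uptake by coverage, and no test, alpha or standard deviation for these comparisons. The check is first a reading of the text, then an illustration on assumed inputs.

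**Text**

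1. Insurance may affect access and cost (Participants WNP eligibility), and cost may limit use (Limitations and opportunities).
2. Program entry is open to every insurance type, so coverage among WNP patients can be mixed.
3. The matching rule is stated: gender, and age within 10 years. It is a fixed design choice and not a detail left open.
4. Similarity is asserted between clinics. The WNP cohort is a selected part of its clinic: patients who want to lose weight, were referred by a primary care provider and completed a visit. Coverage could plausibly influence those steps, though the article does not say that it does.
5. Difference-in-difference is stated for weight only. It removes a fixed difference in weight level. It does not remove a coverage difference that changes the treatment received after baseline and, through that, the weight change.

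**Illustration with no true program effect**

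Let c be the covered share of a cohort, h the medication uptake if covered and l the uptake if not.

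- Expected use = c × h + (1 − c) × l.
- Spurious difference = (coverage gap) × (h − l).

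Example: the comparison cohort is 50% covered, h = 20%, l = 5%. Its expected use is 0.5 × 20 + 0.5 × 5 = 12.5%. With 60%, 70% or 80% of WNP patients covered, their expected use is 14.0%, 15.5% or 17.0%. The differences are 1.5, 3.0 and 4.5 points, and the ratios 14.0/12.5 = 1.12, 15.5/12.5 = 1.24 and 17.0/12.5 = 1.36.

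The table gives the spurious difference in points over a wider range. In brackets is the chance of a nominally significant result favoring the program, where it was calculated. That chance assumes 150 per cohort (the article expects about 150 WNP patients in year one; an equal comparison cohort is assumed), two independent groups, mean coverage of 60% and two-sided alpha of 0.05. With no gap it is 2.5%.

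| Uptake if covered / not | Gap 10 points | Gap 20 points | Gap 30 points |
|---|---|---|---|
| 15% / 10% | 0.5 | 1.0 | 1.5 |
| 20% / 5% | 1.5 (5.6%) | 3.0 (11.3%) | 4.5 (20.1%) |
| 30% / 5% | 2.5 (7.8%) | 5.0 (19.0%) | 7.5 (36.8%) |
| 40% / 10% | 3.0 (8.3%) | 6.0 (21.1%) | 9.0 (41.1%) |

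One entry worked by normal approximation, for 20%/5% and a 20-point gap. Use is 0.70 × 20 + 0.30 × 5 = 15.5% against 0.50 × 20 + 0.50 × 5 = 12.5%. The standard error is √[(0.155 × 0.845 + 0.125 × 0.875)/150] = 0.040. The chance is about Φ(0.030/0.040 − 1.96) = Φ(−1.21), or 11%.

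**Weight**

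Assume further that treated patients lose 5 percentage points more weight and that the SD of weight change is 6 points. The spurious weight difference is 5 × the spurious difference in use. For the last three rows this runs from 5 × 0.015 = 0.075 to 5 × 0.09 = 0.45 percentage points. The standard error is 6 × √(2/150) = 0.69, so the upper-tail chance runs from Φ(0.075/0.69 − 1.96) = 3% to Φ(0.45/0.69 − 1.96), about 10%.

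**The case against.** The strongest reply is that the comparison clinic was chosen to reduce this problem: same health system, very close, comparable population. Program entry does not depend on insurance type, and nothing in the article shows that coverage differs between the cohorts. This stands as mitigation. It makes the 20- and 30-point gaps above hard to defend as expectations. It does not balance a referred, attending subset against individuals chosen on gender and age.

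A second reply is that the documented differences matter more. WNP patients want to lose weight, are referred, and must have a weight-related condition, whereas the comparison cohort need only have obesity. That is correct, and handling insurance does not touch it.

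Three stronger readings are tempting, and the article does not support them:

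- *Insurance decides who gets treated.* The text says only that eligibility and cost may differ.
- *The comparisons will be unadjusted.* The article states no adjustment, but a condensed article may leave a covariate list to an analysis plan that is not shown. Only the matching set is firmly fixed here.
- *The Background promises sociodemographic matching that the methods fail to deliver.* The phrase "contemporaneous matched cohort of patients from another primary care clinic with similar sociodemographic characteristics" most naturally describes the clinic, and the methods section is consistent with that. No promise is broken.

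Finally, the Weight Navigator's own attention to insurance and cost is part of the intervention. The possible confounder is the coverage mix at baseline.

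**Conclusion.** The point holds as a minor one. The article names a plausible determinant of treatment use and states a matching rule that omits it, so coverage mix could distort the between-cohort comparisons of engagement, prescriptions and refills. At a 10-point coverage gap, the assumed inputs give 0.5 to 3.0 points of spurious medication use. Larger gaps give more, but the article offers no support for them. The effect on weight change is likely small: under half a percentage point in every scenario calculated, even at a 30-point gap.

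All of these sizes rest on assumed coverage and uptake, and the illustration uses the proportion of users where the plan counts prescriptions and refills. The direction is equally unknown: with lower coverage in the WNP cohort, the bias would run against the program. Feasibility and acceptability are the primary outcomes, and effectiveness is described as preliminary, which also keeps the severity low.

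**What to change.** - In the Change in weight subsection of Clinical impact of the WNP, state that baseline insurance class will be extracted from the electronic health record for both cohorts and reported by cohort.
- Include it as a covariate in the comparisons of weight, referrals, engagement, prescriptions and refills, or as a matching variable where matches allow. In the difference-in-difference model for weight it should enter as an insurance-by-period term (equivalently, as a covariate in a model for change), since a main effect alone is differenced out.
- Because MHealthy is limited to employees, report the comparison of health-system resources with and without it.

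The cost is one more field in an extraction already planned, and slightly fewer exact matches if insurance is used for matching. Covariate adjustment avoids that loss. The change does not address the other cohort differences (referral, desire to lose weight, comorbidity), and the report should say so.
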